### 2.3. Characterization of the Nutritional Properties of Cereals, Especially Ancient Wheat Species (Chemical Study)

#### 2.3.1. Study Design

The experiments will be conducted from November 2024 to December 2025 at (i) the Contact and Structural Mechanics Laboratory (LaMCoS), which features a state-of-the-art lipidomics platform, recognized with the IBiSA label (Infrastructures in Biology, Health, and Agronomy) and ISO9001-certified; and (ii) the Polymer Material Engineering laboratory (IMP).

#### 2.3.2. Outcomes

The primary outcome of this “chemical study” of cereal properties will be to analyze some nutrient and anti-cancer bioactive molecule contents and to study proteins in ancient wheat species, einkorn (*Triticum monococcum* ssp. monococcum), emmer (*Triticum turgidum* ssp. dicoccum), and spelt (*Triticum aestivum* ssp. spelta), in comparison to common wheat species (soft wheat, *Triticum aestivum* spp. aestivum). The secondary outcomes will be to (i) compare the composition between the three ancient wheat species and with common wheat and (ii) evaluate the differences in terms of varieties within each species.

#### 2.3.3. Samples

Twenty-three varieties of ancient wheat species (seven varieties of einkorn, eight varieties of emmer, eight varieties of spelt) and eight varieties of common wheat (soft wheat), which were grown organically in the Lyon region (France) at the Centre de Ressources de Botanique Appliquée (CRBA, Charly) and harvested during summer 2022, will be used. Several of these varieties have also been grown by 6 farmer-bakers involved in the study and located within an 80 km radius around Lyon. The majority of these cereals are local varieties, easily accessible to farmers–bakers in the Lyon region (the seeds came from farms or associations located in the center-east of France).

#### 2.3.4. Chemical Analysis

The quantitative analysis of nutrients and bioactive molecules will be carried out by different methods, in particular inductively coupled plasma mass spectrometry (ICP-MS) and gas chromatography coupled with tandem mass spectrometry (GC-MS/MS). The protein study will be performed combining various physicochemical techniques, such as size exclusion chromatography, light scattering, and rheology.

### 2.4. An Investigation of the Plant-Based Food Consumption Perceived Behaviors Captured in the General Population (Behavioral Study)

#### 2.4.1. Study Design

The “behavioral study” is a mixed cross-sectional study, employing both quantitative and qualitative methodologies. It will be conducted in two steps.

The quantitative phase will involve a survey to assess knowledge, attitudes, and behaviors (KAB) related to the PHD in the general population. The survey will be structured with a total of 35 items (1 item with an open-ended answer and 34 items with closed-ended answers).

This qualitative phase will focus on face-to-face interviews with regular customers of farmers–bakers. These interviews will allow for a deeper exploration of the motivations, behaviors, and profiles of these customers.

Both phases will contribute to a comprehensive understanding of the KAB concerning the PHD, with the quantitative data providing generalizable results and the qualitative interviews offering nuanced insights into the specific population of regular customers of farmers–bakers.

#### 2.4.2. Study Setting

The analysis of the KAB regarding the PHD, the first step of the “behavioral study”, will be conducted between March 2024 and December 2025.

The face-to-face interviews, the second step of the “behavioral study”, will be conducted between March 2024 and May 2024.

#### 2.4.3. Outcomes

The main objective will determine the percentage of people in the general population with attitudes and behaviors corresponding to the PHD.

The secondary outcomes will be as follows:-To assess the general population’s knowledge of the PHD;-To identify determinants of the respondents with attitudes and behaviors corresponding to the PHD;-To identify obstacles and levers among regular consumers of farmers–bakers regarding their consumption of plant-based foods.

#### 2.4.4. Study Population and Inclusion Criteria

For the KAB questionnaire, the target population will be (i) people over 18-years-old, (ii) people able to read and understand the French language, (iii) users (patients and professionals) of the central kitchen of the Hospices Civils of Lyon (HCL), and (iv) customers of farmers–bakers.

For the face-to-face interviews, the target population will be the regular customers of farmers–bakers.

#### 2.4.5. Sample Methodology

For the KAB questionnaire, the population will be recruited on the basis of a convenience sampling methodology by distributing the questionnaire to users of the central kitchen of the HCL and to customers of farmers–bakers.

For the face-to-face interviews, the target population will be recruited thanks to the farmers–bakers already identified in the chemical study as suppliers of ancient wheat species (einkorn, emmer, spelt) and common wheat.

#### 2.4.6. Sample Size

For the KAB questionnaire, considering a population of more than 10,000 users of the HCL central kitchen, with a confidence level of 95% and a margin of error of 5%, an estimated return of 383 questionnaires is deemed representative of the population.

For the face-to-face interviews, it is recognized that in the case of a homogeneous sample, (i) the first five to six participants produce the majority of new information in the dataset, while little information is obtained from subsequent participants; (ii) data from the first ten participants identify 80–92% of the information [63], and when the sample size is close to 20 interviews, little new information will be collected [64]. Thus, about 12 participants should allow for data saturation [65].

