
The BIOQUALIM project has several limitations. Firstly, the contribution of plant proteins to the diet is focused on einkorn in the clinical study and on ancient (einkorn, emmer, spelt) and soft wheat species in the chemical study, whereas many other sources of plant proteins exist. Secondly, the sample size is small and the single-arm design of the clinical study is a limitation, as the aim is to provide a proof of concept, since no data currently exist on the effect of diet modification on the oral interdental microbiota. Thirdly, the behavioral study will use convenience sampling which could induce some bias, even if it appears very low. Fourthly, the BIOQUALIM project is focused on ancient wheat species grown in the Lyon region (France), which has its own specificities (soils, climate, etc.). Fifthly, the questionnaires from the behavioral study will be realized online, which could result in misunderstandings of the questions due to the lack of direct supervision. Sixthly, in the clinical study, despite precautions and participants’ involvement in culinary workshops, there will be a possibility that some participants may not have adhered to the prescribed spelt consumption, potentially affecting dietary compliance. Finally, factors beyond diet, such as oral hygiene and physical activity, may also influence the oral microbiota, adding complexity to the clinical study’s outcomes.

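### The behavioral survey claims a general-population percentage and representativeness that a convenience sample, sized only for hospital-kitchen users, cannot deliver

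*Protocol article*

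**What the plan says.** Section 2.4.3 sets the main objective of the questionnaire survey: to "determine the percentage of people in the general population with attitudes and behaviors corresponding to the PHD". Section 2.4.1 describes the two phases of the study "with the quantitative data providing generalizable results" and the interviews adding depth on farmer-baker customers.

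Section 2.4.4 describes the target population as French-reading adults who use the HCL central kitchen (patients and professionals) and customers of farmer-bakers. Under section 2.4.5 they are "recruited on the basis of a convenience sampling methodology", by handing the questionnaire to those two groups.

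Section 2.4.6 bases the sample size on a single group, "considering a population of more than 10,000 users of the HCL central kitchen", at 95% confidence with a 5% margin, and concludes that "an estimated return of 383 questionnaires is deemed representative of the population". The limitations paragraph in section 3 concedes that the study uses "convenience sampling which could induce some bias, even if it appears very low". It gives no evidence for the last clause.

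**The concern.** A margin of error from the single-proportion formula describes random sampling error when respondents are drawn at random from one defined population. Neither condition is met here. There is no random draw, and the population in the formula (kitchen users) is neither the one sampled (kitchen users plus farmer-baker customers) nor the one in the objective (the general population).

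The second source matters because its customers plausibly differ on the outcome. Section 2.4.5 identifies the farmer-bakers as suppliers of einkorn, emmer and spelt as well as common wheat. Section 2.4.1 treats their regular customers as a specific population worth separate study, and section 2.4.3 singles them out for obstacles and levers to eating plant-based foods. No quota or mix between the two sources is stated, so any percentage that combined them would move with the recruitment mix.

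At stake is the headline result of one of the four BIOQUALIM studies. Section 3 expects the project's results to support recommendations for policy and practice, and it foresees targeted health promotion following the survey of eating habits and knowledge.

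**Working it through.** **Inputs.** Confidence 95% (z = 1.96), margin d = 0.05, population N above 10,000 and 383 returns, all from section 2.4.6. The expected proportion is not stated; p = 0.5, the worst case, is assumed.

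**1. Reproducing the 383.**
- Infinite population: n0 = z²p(1−p)/d² = 1.96² × 0.25 / 0.05² = 384.2.
- Finite-population correction: n = n0 / (1 + (n0 − 1)/N). At N = 10,000, 384.16/1.0383 = 370. At N = 20,000, 377. At N = 50,000, 381.2, or 382 rounded up. At N = 100,000, 384.16/1.00383 = 382.7, or 383.

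The text says more than 10,000, so 383 is consistent with a large user population. It is the simple-random-sample formula for one population.

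**2. Populations side by side.**
- Objective (2.4.3): the general population.
- Sample (2.4.4, 2.4.5): a convenience sample of HCL kitchen users and farmer-baker customers.
- Precision calculation (2.4.6): HCL kitchen users only.

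**3. What the 5% covers.** At n = 383 the half-width is 1.96 × √(0.25/383) = 5.01 points of random error. With bias b and SE = √(0.25/383) = 0.0255, the coverage of the nominal 95% interval is Φ(1.96 − b/SE) − Φ(−1.96 − b/SE). For assumed biases:
- b = 2 points: about 88%
- b = 5 points: about 50%
- b = 10 points: about 2.5%

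**4. Sensitivity to the recruitment mix, if the sources were pooled (all rates and shares assumed).** Let 20% of kitchen users meet the definition, and let s be the share of returns from customers.
- Customer rate 60%: pooled = 0.2(1 − s) + 0.6s, which is 24%, 30% and 40% at s = 10%, 25% and 50%.
- Customer rate 40%: pooled = 0.2(1 − s) + 0.4s, which is 22%, 25% and 30%.

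The shift from the kitchen-user rate is 2 to 20 points. The upper end needs both a 40-point gap and half of the returns from customers.

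**5. Nominal half-width by source (p = 0.5).**
- All 383 are kitchen users: 5.0 points.
- Customers supply half of the 383, leaving n = 192 kitchen users: 1.96 × √(0.25/192) = 7.1 points.
- Those 192 split equally into patients and professionals, n = 96 each: 1.96 × √(0.25/96) = 10.0 points.

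**The case against.** The best defence is that the article is open about its method. Section 2.4.5 names convenience sampling and section 3 warns of bias. The survey is one of four studies, and nothing in the article makes the clinical study's primary outcome depend on it. All of this is true. But the warning minimizes the bias without support, and it leaves the claims in sections 2.4.1 and 2.4.6 standing.

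Several stronger readings are tempting but are not supported:

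- *The general-population figure carries a 5% margin.* The article does not say so; section 2.4.6 attaches the margin to kitchen users. It is nevertheless the only precision basis given for the objective, and under convenience sampling it does not measure total error for kitchen users either.
- *The two sources will be pooled.* A single percentage and a single return target suggest it, but no sentence states it. Section 2.4.8 provides for stratification and subgroup comparison. It gives age group as an example and does not exclude recruitment source.
- *Precision for kitchen users is already lost.* The 7.1 points apply only if customers count towards the 383. If they come on top, kitchen users keep the nominal 5 points.
- *Customers are selected on the outcome itself.* They are recruited for where they buy, from bakers who also supply common wheat, and the outcome concerns attitudes and behaviors matching a whole-diet pattern. A correlation is plausible, but its size is unknown.

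**Conclusion.** The plan is wrong as written on this point. It claims a general-population percentage, generalizability and representativeness, and its sampling supports none of them at any number of returns. The fault lies in the inference drawn from 383, not in the figure itself.

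This conclusion rests on the article's text alone and needs no assumed rate. The amount of bias cannot be determined from the article: the coverage figures and the 2-to-20-point shift are illustrations on assumed values, and the shift arises only if the sources are combined. The half-widths of 7.1 and 10.0 points follow from the formula, but they depend on p = 0.5, on whether customers count towards the 383 and on equal splits.

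**What to change.** - Section 2.4.3: restate the main objective as the percentage among respondents, reported separately for HCL kitchen users and farmer-baker customers. Label any combined figure as describing respondents only.
- Sections 2.4, 2.4.1, 2.4.3 and 2.4.6: withdraw the references to the general population, representativeness and generalizability as claims for this estimate.
- Section 2.4.6: state whether customers count towards the 383. Describe 5% as the nominal random-sampling half-width for 383 kitchen-user returns, and note that it widens to about 7.1 points at n = 192 and about 10 points at n = 96.
- Section 3: delete the clause that calls the bias very low.

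Weighting to regional margins is not a substitute. Section 2.4.8 covers respondents' own characteristics, the regional margins are not in the article, and weighting would not remove selection on unmeasured interest in diet.

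The changes need rewording and a table by source, with no new recruitment. The cost is a narrower claim and clearly wider intervals by source: 7.1 points is about 40% wider than 5 (7.1/5 = 1.42), and 10 points is twice as wide.

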#### 2.4.7. A Description of the Procedure, Data Collection, and Interviews

For the KAB questionnaire, a self-administered questionnaire will be developed by the research team in a transdisciplinary manner based on the Food Choice Questionnaire [66]. The KAB questionnaire will be tested by 10 persons who will not be included in the final study. The questionnaire will take an estimated 12 min to complete. It will be available in paper or digital version with a QR code accessible on a tablet, PC, or smartphone (Supplementary File S1). All questions are mandatory.

For the face-to-face interviews, participant experiences will be collected by a qualitative study specialist using a semi-structured individual interview guide. This guide will be developed specifically because no pre-used or validated models were identified in the literature. Therefore, it was conceived by the research team composed of specialists in public health and psycho-social sciences and students in agronomy. Each member established a list of relevant questions, and then all proposals were pooled and discussed until consensus was reached on the questions to include in the interview guide. The guide will be tested during two interviews with individuals from the studied population who are not participating in the final study. This test will evaluate the time needed for the interview, check the reliability and understanding of each question, and adapt the guide if necessary. The interview guide will be composed of four sections: (i) knowledge of nutrition, (ii) plant-based protein intake, (iii) eating habits, and (iv) changes in eating habits.

#### 2.4.8. Data Analysis

A univariate analysis will describe all of the characteristics of the respondents of the KAB study including socio-demography, income level, and place of residence. Some covariates of interest will be identified for stratification (e.g., age group). The sub-groups will be compared to identify major differences or similarities. A multivariate analysis will evaluate the determinants of the outcomes (K, A, and B), especially the socio-spatial disparities in terms of the PHD. Socio-demographic data (age, gender, socio-professional characteristics) and data relating to the place of residence will also be integrated (social deprivation, population density, type of agriculture in the municipality, and type of municipality thanks to the GeoClasH classification) [67]. The statistical analysis will be performed using the software SPSS 12.0 (SPSS Inc., Chicago, IL, USA).

The analysis of the face-to-face interviews will follow the methodological framework proposed by Braun and Clarke [68], which consists of a thematic analysis. First, the recordings of the conversations will be transcribed verbatim and checked to track the exact course of the interview, indicating all components of the communication to understand the interactions (including laughter, hesitations). Second, two researchers will carry out open coding with an in-depth reading of each verbatim transcription. They will use a mixed content analytic method: inductive and deductive. Third, the two researchers will discuss the initial codes until they reach an agreement and draw up the first codebook. In case of divergent opinions, a third researcher who is a member of the research team will be consulted. Fourth, researchers will use the structure of this codebook to analyze the remaining responses, remaining open to the inclusion of new codes or the refinement of existing ones. Fifth, the final structure with themes and subthemes will be finalized, and occurrences will be measured to weigh the results. Reliability during thematic data analysis will be ensured by systematically storing raw data, reporting detailed notes on the development and organization of concepts and themes, establishing consensus on the themes, providing precise descriptions of the context, and describing the coding and analysis process [69,70]. EXCEL^®^ 2019 MSO software will be used for data analysis.

### 2.5. Evaluation of the Impact of Health Promotion Programs Focusing on the PHD, Using Plant-Based Cooking Workshops to Provide Peer Support, on Cancer Patients (Psycho-Social Study)

#### 2.5.1. Study Design

The “psycho-social study” will be a cohort observational study that aims to determine if peer-support (led by a former patient) plant-based cooking workshops could be facilitators in promoting the PHD and reducing barriers to preparing and consuming it, specifically for cancer survivors.

#### 2.5.2. Study Setting

The “psycho-social study” will be conducted between February 2024 and December 2025.

#### 2.5.3. Outcomes

The primary outcome will be to analyze the impact of peer-support plant-based cooking workshops on improving post-treatment cancer patients’ knowledge of the PHD and their intention to introduce protein-rich cereals (einkorn, emmer, and spelt) into their diet.

The secondary outcomes will be as follows:-To analyze the satisfaction of post-treatment cancer patients regarding the introduction of protein-rich cereals into their diet;-To raise patients’ awareness of micro-environmental health (reading labels, the benefits of plant-based food rich in protein and grown organically) and macro-environmental health (agricultural systems and their link with health, One Health approach);-To analyze the perception of social support and the knowledge and confidence gained through the cooking workshops.

#### 2.5.4. Study Population

This “psycho-social study” will include participants who (i) are over 18 years of age, (ii) have suffered from cancer in all specialties and are post-therapeutic (<2 and 5 years after the end of treatment for solid tumor and hematology, respectively), and (iii) have an oncological performance status (PS) assessment <2 [71]. The exclusion criteria will be as follows: (i) to present contraindications to the consumption of whole grains, pulses, fruits, and vegetables and (ii) to be unavailable on the workshop dates.

#### 2.5.5. Sample Size

To optimize the intervention experience and maintain sufficient interactivity between all members of the group that will be led by two patient partners, groups of 8 participants will be set up. Participants will be recruited through purposive sampling [72].

#### 2.5.6. A Description of the Procedure and Data Collection

Participants will participate in six 2-h themed cooking workshops spaced 2 weeks apart in a specially equipped therapeutic kitchen (4). During each workshop, two recipes will be performed using either einkorn, emmer, or spelt in different forms (whole grains, couscous grains, flakes, flour, and crushed grains). An educational summary sheet and recipe sheets will be provided to each participant at the end of each workshop.

For these cooking workshops, an evaluation process based on the Kirkpatrick model [73] will be used to evaluate the health benefits of these workshops, according to the 4 levels described below.

Level 1 will evaluate the immediate reaction of participants (pedagogical evaluation of the workshops) via one questionnaire given at the end of each workshop and face-to-face interviews (Supplementary File S2). This questionnaire will be composed of seven questions (six closed questions and one open question).

Level 2 will evaluate the acquisition of knowledge/skills (food literacy, in particular the ability to find information on food and cancers, to understand it critically; “empowerment”, in particular increased confidence regarding the consumption of plant proteins and one’s own cooking skills). Participants will answer one questionnaire before and at the end of the cooking workshops series composed of 13 closed questions (Supplementary File S3).

Level 3 will evaluate the modification of cooking and consumption behavioral habits, whereas level 4 will evaluate patient satisfaction with (i) their general state of health (Patient-Reported Experience Measures, PREMs) [74] and with (ii) the adequacy of these cooking workshops in relation to their needs at the end of their treatment (tertiary prevention) in order to ensure the reproducibility of the workshops. These two levels will be evaluated during semi-structured individual interviews. The interview guide was developed for this study by the research team on the consensus principles. This interview guide (Supplementary File S4) is composed of four sections: (i) the “theme of cancer food” that aims to explore food representations by cancer patients, (ii) the “benefits of cooking workshops” that aims to identify perceived social support, self-efficacy, and representations about the group dynamics, (iii) the “after the cooking workshops” that aims to analyze behavioral intention to introduce einkorn, emmer, or spelt cereals into eating habits, and (iv) the “final questions” that aims to collect satisfaction level, suggestions, and opinions about the workshops. This interview guide will be tested during one interview with a patient belonging to the study population but not participating in the study. This test will assess the time needed for the interview and verify the consistency and the good comprehension of each question, enabling adjustments if necessary. To consolidate knowledge input, participants will be invited to attend a seminar after the six workshops where a specialist will provide information about these protein-rich cereals.

